## Abstract

**Background:**

Achilles tendinopathy is one of the most frequent conditions affecting runners. Exercise-based interventions are the main treatment options for Achilles tendinopathy; however, the ideal exercise dosage remains unknown.

**Objective:**

The objective of this study is to investigate the effects of a moderate-load exercise intervention compared to a high-load exercise intervention in runners with Achilles tendinopathy in terms of pain, symptom severity, quality of life, muscle strength, and function.

**Methods:**

Sixty amateur runners will be randomly allocated to one of two groups: high-load exercise group (HLG) and moderate-load exercise group (MLG). The HLG will start the treatment with calf exercises with 55% of 1 repetition maximum (1RM) and progressively increase the exercise load in 12 weeks to 90% 1RM. The MLG will perform exercises with 55% 1RM during the 12 weeks of intervention. The RM load will be reassessed every 2 weeks, and the total training volume (total repetitions and tendon time under tension per week) will be the same in both groups. Both groups will also perform strengthening exercises for the quadriceps and gluteal muscles. The primary outcome will be symptom severity (Victorian Institute of Sport Assessment−Achilles), which will be evaluated at baseline, at week 6, at week 12 (end of intervention), and 6 months after the intervention. Pain will be evaluated using the visual analogue scale during the same time points. Secondary outcomes will include peak isometric strength of ankle, knee, and hip muscles, function of plantar flexor muscles, quality of life, and perception of improvement. Results will be analyzed under the intention-to-treat principle using generalized estimating equations (GEE) and Bonferroni-adjusted post hoc tests.

**Discussion:**

This will be the first randomized controlled trial comparing high-load exercises versus moderate-load exercises in individuals with Achilles tendinopathy applying equal training volume.

**Trial registration number:**

RBR-4vwy5xj

## Introduction

Achilles tendinopathy is a common musculoskeletal condition affecting both active and sedentary individuals [1]. The incidence of Achilles tendinopathy is 2–3 per 1,000 individuals in the general population and is even more common in physically active individuals [2]. In a cohort study with 3,379 participants carried out among recreational runners, the incidence of Achilles tendinopathy was 4.2%, and of these, 64% had mid-portion Achilles tendinopathy [3]. In elite distance runners, the prevalence of Achilles tendinopathy in their lifetime can be as high as 52% [4]. Males have also been shown to be more affected by Achilles tendinopathy than females [3]. In addition to being highly prevalent, Achilles tendinopathy can have a substantial impact on an individual’s long-term health and quality of life [5].

Currently, interventions involving exercises with gradual load progression for clinical improvement and positive tendon adaptation are considered the first-line treatment for Achilles tendinopathy [1,6,7]. The classic Alfredson eccentric training protocol remains one of the most popular interventions among clinicians [8]. However, patient recovery rates with traditional interventions, such as the Alfredson protocol, seem to be far from ideal [9–12]. A few studies report that between 20‒40% of patients experience unsatisfactory results after 10 years of treatment [9,10] and that only 39% of patients treated with the Alfredson protocol are asymptomatic after 5 years [11]. A recent systematic review also concluded that there is low quality of evidence that the Alfredson protocol yields superior results to wait-and-see and passive interventions [12]. Therefore, there is a need for research on the effects of other treatment approaches that investigate the effects of other rehabilitation interventions for Achilles tendinopathy with long-term evaluations.

A few studies have evaluated the variation in progressive loading parameters [13,14], such as the number of repetitions, sets, frequency, and load, to find an ideal exercise dose and load magnitude during interventions in patients with tendinopathy [15]. Recently, Arampatzis et al. [16] suggested that when comparing exercise programs with the same volume, but with different loads, only protocols with greater load produce adaptations in the tendons, such as increased stiffness and increased cross-sectional area in people with healthy Achilles tendons. It is believed that this occurs because high-magnitude contractions cause deformation (strain) of the tendon within the range considered ideal (between 4.5 and 6%) for positive mechanical and morphological adaptations [16]. High-load exercises (90% of 1 repetition maximum (1RM)), in addition to improving strength and generating hypertrophy, can cause an effective mechanical stimulus in the Achilles tendon that stimulates beneficial adaptations in the tissue, causing improvement in the mechanical properties of healthy Achilles tendons [16,17]. The same research group has observed, in a non-randomized controlled study, that an intervention involving isometric exercises performed at 90% 1RM resulted in more structural adaptations in the Achilles tendon of patients with Achilles tendinopathy when compared with the Alfredson protocol and with passive treatments [18]. However, recent evidence suggests that tendon structural adaptations also occur in tendinopathic patellar tendons in response to moderate-load progressive exercises (55% 1RM) [13,19,20].

To our knowledge, however, the effects of exercises with different load magnitudes on individuals with Achilles tendinopathy remain unknown. The primary objectives of the study will be to verify the short-term (6 and 12 weeks) and long-term (6 months) effects of moderate-load calf exercises compared to high-load calf exercises in amateur runners with Achilles tendinopathy in terms of pain and severity of symptoms. The secondary objectives will be to verify the effect of the interventions on strength, muscle function, and quality of life in runners with Achilles tendinopathy.

## Materials and methods

### Study design and trial status

This is the protocol for a randomized, blind, parallel group (1:1) controlled trial comparing two exercise programs for runners with Achilles tendinopathy. The study will be carried out at the Department of Physiotherapy at the Federal University of Rio Grande do Norte (UFRN) and will follow the guidelines of the Standard Protocol Items: Recommendations for Interventional Trials (SPIRIT) (S1 File) [21]. Participants will be randomized into one of two groups: high-load group (HLG) and moderate-load group (MLG). This clinical trial will be reported following the Consolidated Standards of Reporting Trials (CONSORT) guidelines [22] and the protocol was registered on the Brazilian Registry of Clinical Trials (ReBEC). The recruitment of participants began on June 4^th^, 2024. It is expected that the last participants will be recruited by October 31^st^, 2025. The final data collections will take place in July 2026, and results should be completed by September 2026.

The project (S2 File) was approved by the Research Ethics Committee of Federal University of Rio Grande do Norte, Health Sciences College of Trairi – UFRN/FACISA (process 6729527; CAAE 78022924.3.0000.5568), based on protocol version 2.0, dated March 12, 2024. Evaluators will obtain participants’ signatures on the Informed Consent Form and on the authorization form for voice and image recording. The individuals pictured in “S2_File_ Protocol_approved_by_ethics committee” (Figs 3, 8, 10, 11, 14), “S3_File_Assessment”, and “S4_File_Treatment_Protocol” have provided written informed consent (as outlined in PLOS consent form) to publish their image alongside the manuscript. The results will be disseminated through publications in scientific journals, social media, and presentations at scientific events.

### Eligibility criteria

Recreational male runners aged 18–60 years with midportion Achilles tendinopathy will be included. The clinical diagnosis of midportion Achilles tendinopathy will be performed by registered physical therapists with more than 4 years of practice experience in musculoskeletal physiotherapy. The diagnosis will follow the following criteria: localized pain in the midportion of the Achilles tendon (two to six centimeters above the tendon insertion into the calcaneus) with a minimum duration of three months and a minimum intensity of 3 on the Visual Analogue Scale (VAS), pain during loading activities such as running, and pain on palpation [7,23–25].

Individuals will be excluded if they present (1) exclusively insertional Achilles tendinopathy, (2) a washout period of less than 4 weeks from other treatments, (3) use of corticosteroid injections in the Achilles tendon region, or use of fluoroquinolone antibiotics in the last 12 months [26], (4) other injuries of the affected lower limb in the last 6 months, (5) musculoskeletal surgery on the spine or lower limbs over the previous 12 months, (6) history of Achilles tendon rupture, and (7) systemic diseases that may interfere with tendon health (i.e., rheumatoid arthritis or diabetes) [23].

Participants’ recruitment will be carried out through an active search of registrations of running groups active in the city of Natal, Rio Grande do Norte (Brazil). Online ads in social media (Instagram, WhatsApp, Telegram, Facebook) and printed banners at traditional race locations in the city will be used as advertisement strategies. Runners experiencing Achilles tendon pain will be invited for clinical assessment of possible eligibility.

After eligibility is established, for sample characterization purposes, each participant’s level of physical activity will be assessed using the short version of the International Physical Activity Questionnaire-Short Form (IPAQ-SF) [27], and for the assessment of kinesiophobia, the Brazilian Portuguese version of the Tampa Scale of Kinesiophobia (TSK) will be used [28] at the baseline evaluation.

### Sample size calculation

To determine the study sample size, a calculation was made considering a confidence level (α) of 95%, a power (β) of 80%, and a difference between groups in the Victorian Institute of Sport Assessment-Achilles (VISA-A) at 12 weeks of 14 points [24]. The standard deviation used in the calculations was obtained from a similar clinical trial that used this same variable as the primary outcome [23]. Using this information, calculations for linear mixed models indicated a sample size of 54 individuals (27 per group). Considering a loss of 10%, we reached a total number of 60 individuals, with 30 in each group.

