### Statistical analysis

The data will be analyzed by a researcher who will remain blind to group allocation. The Statistical Package for the Social Science software (version 17.0; SPSS Inc, Chicago, IL) will be used to analyze the results. To assess the normality of data, the Shapiro-Wilk test will be used. Outcome measures will be analyzed using generalized estimating equations (GEE) to identify main effects of group and time, and group-by-time interactions. Bonferroni-adjusted post hoc tests will be used when appropriate. The results will be presented as mean differences and 95% confidence intervals (CI). All data will be analyzed using the intention-to-treat principle, and in the event of missing data, a regression-based imputation technique will be used [55].

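### GEE is fixed for a trial of 54–60 participants with no small-sample correction named; the usual uncorrected robust tests would run above their 5% level

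*Protocol article*

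**What the plan says.** Under Sample size calculation the protocol article reports that "calculations for linear mixed models indicated a sample size of 54 individuals (27 per group"), for a difference in "Victorian Institute of Sport Assessment-Achilles (VISA-A) at 12 weeks of 14 points". The loss allowance follows: "Considering a loss of 10%, we reached a total number of 60 individuals, with 30 in each group".

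Under Statistical analysis the method is a different one: "Outcome measures will be analyzed using generalized estimating equations (GEE"), with group, time and their interaction as the effects of interest. Bonferroni-adjusted post hoc tests and mean differences with 95% confidence intervals follow. The abstract says the same: "using generalized estimating equations (GEE) and Bonferroni-adjusted post hoc tests". The software is SPSS version 17.0, and missing data are to be handled by regression-based imputation.

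Under Outcomes, VISA-A and VAS pain are measured four times (baseline, week 6, week 12 and 6 months after the end of treatment). The secondary outcomes are measured at baseline and week 12, and GROC at week 12 only.

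The article does not name a GEE covariance estimator, a small-sample correction or a reference distribution. It does not link the model used for sizing to the model used for analysis.

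**The concern.** The usual GEE test divides an estimate by a sandwich standard error and refers the result to a normal or chi-square distribution. Both steps are justified by a large number of clusters, and each participant is a cluster here. With 27–30 participants per group the uncorrected sandwich variance is biased downwards, and the chi-square reference ignores the uncertainty in that variance. Both faults act in the same direction: too many false positives and intervals that are too short.

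The error grows with the number of parameters tested jointly. It is therefore largest for the interaction test on the four-visit outcomes, which include the primary outcome. At stake is whether a nominal 5% test of whether the two load programmes differ over time is in fact a 5% test.

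**Working it through.** **Inputs.** From the article: 27 evaluable participants per group, 30 randomised; four visits for VISA-A and VAS pain, so the group-by-time test has 4 − 1 = 3 df. Assumed: two-sided 5% level, complete data, normal outcomes with the same covariance in both groups, a separate mean for each group and visit, and the uncorrected sandwich variance with a chi-square/z reference.

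**The plan's own figures.**
- Loss allowance: 54/0.90 = 60. This reproduces.
- The 54 cannot be fully reproduced, because the SD is cited ("The standard deviation used in the calculations was obtained from a similar clinical trial") but not given as a number. For a simple two-group comparison by normal approximation, n per group = 2(1.960 + 0.842)² SD²/14². Setting n = 27 gives SD ≈ 18.4 (18.0 by t-test). SD 16 gives 42 in total, 18 gives 52, 19 gives 58 and 20 gives 66. So 54 is consistent with an SD of about 18, and nothing here shows it to be wrong.

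**Exact error of the uncorrected test.** In this setting the GEE estimates are differences of cell means, and the sandwich variance is (n − 1)/n times the unbiased one. The Wald statistic W is then Hotelling's T² multiplied by n/(n − 1). With d = 2n − 2:

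P(W > 7.815) = P( F(3, d − 2) > 7.815 × (n − 1)/n × (d − 2)/(3d) )

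- n = 30: 7.815 × (29/30) × 56/(3 × 58) = 2.431; P(F(3,56) > 2.431) = 7.46%.
- n = 27: 7.815 × (26/27) × 50/(3 × 52) = 2.412; P(F(3,50) > 2.412) = 7.77%.

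For a single contrast the effective t cut-off is 1.960 × √((n − 1)/n):

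- n = 30: 1.960 × 0.9832 = 1.927; two-sided P on 58 df = 5.89%.
- n = 27: 1.960 × 0.9813 = 1.923; two-sided P on 52 df = 5.99%.

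**Interval length for a single contrast**, relative to the correct t interval:

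- n = 30: 1.927/2.002 = 0.963.
- n = 27: 1.923/2.007 = 0.958.

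The intervals are about 4% too short, with coverage of about 94.1% and 94.0%.

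**Simulation** (complete data, 100,000 trials per scenario, exchangeable correlation 0.3, 0.5 and 0.7 and AR(1) 0.6):

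| Test at nominal 5% | 27 per group | 30 per group |
|---|---|---|
| Interaction, 3 df, uncorrected | 7.7–7.8% | 7.4–7.6% |
| Week-12 contrast, uncorrected | 5.9–6.0% | 5.9–6.1% |
| Both, df-corrected variance with F/t reference | 4.9–5.1% | 5.0–5.2% |

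**Actual GEE fits** (exchangeable working correlation 0.5, 10% random dropout from week 12, no imputation, 1,500 trials, simulation standard error about 0.6–0.7 points):

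| Covariance, chi-square/z reference | Interaction, 27 / 30 | Week-12 change contrast, 27 / 30 |
|---|---|---|
| Uncorrected robust | 8.1% / 8.3% | 6.3% / 6.5% |
| Bias-reduced | 5.9% / 6.9% | 4.9% / 5.2% |

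Correcting the variance alone is enough for the single contrast. For the joint test the reference distribution must change as well.

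**The case against.** The strongest objection is that the article does not say which covariance estimator will be used, and such detail is commonly left to an analysis plan or to the full protocol. That stands as a limit: the figures are conditional on the usual uncorrected version. It does not remove the point. The article itself fixes GEE at this sample size, and standard inference for that method is liberal here. A model-based exchangeable test without a degrees-of-freedom correction still gave about 5.9–6.2% for the interaction.

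A second objection is that the effect is small where it matters most. This also largely stands. The trial is sized on the 12-week difference, where the error is about 6%. For three or four Bonferroni-adjusted between-group contrasts (number of contrasts and correlation 0.5 assumed) the simulated familywise error is close to 6%. The 7.5–7.8% applies only to VISA-A and VAS pain. The two-visit secondary outcomes have a 1-df interaction, and GROC has none.

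Three stronger readings are tempting and are not supported:
- *That the switch from mixed model to GEE makes 54 the wrong number.* For a continuous outcome compared at one visit the two methods need nearly the same sample, and no shortfall in power is shown.
- *That GEE fails here because it needs data missing completely at random.* That applies to GEE on the observed data only, and the article plans imputation. Whether that imputation is adequate is a separate question.
- *That GEE must be replaced.* A corrected GEE also addresses the error. The mixed model does so only with small-sample degrees of freedom, which the sample size section does not mention either. GEE's weaker distributional assumptions are a legitimate reason to prefer it for bounded scores and for heel-rise counts.

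**Conclusion.** The point holds in conditional form. If the uncorrected robust Wald tests are used, the interaction test on the four-visit outcomes has a type I error of about 7.5–7.8%, roughly 1.5 times nominal. The 12-week contrast has about 6%, and its 95% intervals are about 4% too short. These figures assume complete, normal data and an estimator that the article does not name. The random-dropout simulation, without imputation, gave somewhat higher values. The differing models for sizing and analysis are an unexplained inconsistency, not evidence that the sample size is wrong. This is a modest fault with a cheap remedy.

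**What to change.** In Statistical analysis, specify one of two routes:

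1. Keep GEE, with a bias-corrected sandwich variance **and** a t/F reference distribution. The joint interaction test needs both.
2. Analyse the continuous outcomes with the linear mixed model already named for sizing: REML, unstructured covariance over visits, and Satterthwaite or Kenward-Roger degrees of freedom.

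State in Sample size calculation how the model used there relates to the one chosen, and give the SD. Confirm that the software and version named in the article support the chosen method, and name another package if they do not.

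No visit, participant or treatment changes. The cost is analysis wording and intervals about 4% wider than the uncorrected ones (1/0.963 = 1.04; 1/0.958 = 1.04). The mixed model also relies on approximately normal residuals, which should be checked for bounded scores such as VISA-A and the 0–10 VAS.

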### Randomization and strategies for minimizing bias

The randomization of participants will be generated using a sample randomization system (block of four) creating a list of random numbers (http://www.randomization.com). An independent researcher who will not be involved with assessments, interventions, or data analysis will be responsible for generating the list. From this list, a set of opaque envelopes will be created and sealed, ensuring allocation concealment.

The evaluators will remain blind to the groups and will perform all study assessments. To ensure blinding, they will not participate in the interventions, and participants will be instructed not to discuss details of their intervention with the other participants or the evaluator. Participants will be randomized at the beginning of the first in-person intervention session. The interventions will be carried out at the Department of Physiotherapy of the Federal University of Rio Grande do Norte (UFRN) and/or local gyms and will be supervised by experienced physiotherapists.

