In addition to specific exercises for the triceps surae, both groups will receive strengthening exercises for the muscles of the kinetic chain (i.e., quadriceps and gluteus maximus), which are synergists of the triceps surae during running and have been shown to have strength deficits in individuals with Achilles tendinopathy [45,46]. These exercises will be performed following the recommendations for strength training in resistance-trained individuals from the American College of Sports Medicine (ACSM) [47]. Specifically, these exercises will be performed in the following manner: in the first phase (1^st^ − 4^th^ weeks), participants will perform the exercises in 3 sets of 12 repetitions with 60% 1RM, in the second phase (5^th^ − 8^th^ weeks) they will perform the exercises in 3 sets of 10 repetitions with 70% 1RM, and in the third phase (9^th^ − 12^th^ weeks) they will perform the exercises in 3 sets of 8 repetitions with 80% 1RM [47] (S4 File).

Every two weeks, during the supervised session, a 10RM test will be performed to estimate 1RM and adjust training loads of all exercises accordingly [48,49]. In exercises where resistance will be provided by an elastic band, two levels of elastic resistance lower than 1RM will be established as the initial load, and the load will progress by increasing 1 level of elastic resistance [50].

Participants of both groups will be instructed to refrain from performing intense physical activities that may overload the Achilles tendons (i.e., daily running) during the duration of the study. If they are unwilling to do so, they will be asked to refrain from such activities for the first 3 weeks of treatment [23]. After this period, they will be allowed to resume their running routine using the pain monitoring model as a guide, i.e., avoid running distances/intensities that cause their pain to increase to more than 4/10 during or in the day after the run [51].

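### A single fixed block of four, with allocation at a first session supervised by unblinded physiotherapists, leaves up to one allocation in three deducible, so sealed envelopes alone do not ensure concealment

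*Protocol article*

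**What the plan says.** The section on randomization and minimizing bias names one block size: "The randomization of participants will be generated using a sample randomization system (block of four) creating a list of random numbers". Two safeguards follow. The first is independent list generation: "An independent researcher who will not be involved with assessments, interventions, or data analysis will be responsible for generating the list". The second is a set of sealed opaque envelopes made from that list, which the article says ensures allocation concealment. On timing it says "Participants will be randomized at the beginning of the first in-person intervention session". Evaluators are blind, perform all assessments and take no part in the interventions. Sessions take place at the university department and/or local gyms under physiotherapist supervision.

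The design section gives the ratio: "This is the protocol for a randomized, blind, parallel group (1:1) controlled trial comparing two exercise programs for runners with Achilles tendinopathy". No stratification factor and no second block size is named. The sample size section gives the total: "Considering a loss of 10%, we reached a total number of 60 individuals, with 30 in each group".

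The article does not say who holds or opens the envelopes, whether they are numbered, what fixes the order of their use, or whether the block size is kept from the therapists.

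**The concern.** Sealed opaque envelopes and an independent list generator stop anyone reading the list. They do not stop anyone working out the next entry from the entries already used. With a fixed block of four, the last place in every block is determined by the first three, and the third place is determined whenever the first two match.

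The supervising physiotherapists learn the arm of each participant they treat, because the programs differ from the start (Table 1 gives 15 against 17 repetitions per set in weeks 1–2). Randomization takes place at the session they supervise. If envelopes are used in order of attendance, which the article neither states nor excludes, the order in which assessed runners come to that session decides who receives a deducible allocation.

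The trial has 60 participants, a self-reported primary outcome (VISA-A) and two arms whose intensity is obvious to those delivering them. If runners with worse symptoms tended to be scheduled into one arm, the VISA-A comparison would carry that selection.

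**Working it through.** **Inputs.** Block size 4 (randomization section); ratio 1:1 (design section); 54 participants before a 10% loss (sample size section).

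**The plan's own total.** 54 / (1 − 0.10) = 60, as stated. 60 / 4 = 15 complete blocks. The article gives no figure for predictability.

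**Deducible allocations.** A balanced block of four has six equally likely orders. The allocations fixed by earlier ones in the same block number:

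- AABB 2, ABAB 1, ABBA 1, BAAB 1, BABA 1, BBAA 2
- Mean: (2 + 1 + 1 + 1 + 1 + 2) / 6 = 8/6 = 4/3 per block
- Share: (4/3) / 4 = 1/3 = 33.3%
- Over 15 blocks: 15 × 4/3 = 20 of 60, with minimum 15, maximum 30 and SD √(15 × 1/3 × 2/3) = 1.8

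**Best-guess accuracy.** The chance of a correct guess at places 1 to 4 is 1/2, 2/3, 2/3 and 1. The mean is (17/6) / 4 = 17/24 = 70.8%, against 50% with no information.

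**Partial visibility.** Suppose an observer knows the block size and the block boundaries but sees each earlier allocation only with probability f. Certainty then requires having seen both members of the exhausted arm, which has probability f². Place 4 contributes f² and place 3 contributes f²/3, so the share is (f² + f²/3) / 4 = f²/3.

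| Share of allocations seen | Share deducible |
|---|---|
| 100% | 33% |
| 75% | 19% |
| 50% | 8% |
| 25% | 2% |

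Simulation gave the same values.

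**Varying block sizes.** This was simulated over 60 allocations, for an observer who knows the possible sizes and the full history but not the order of the sizes.

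| Scheme | Deducible | Best guess correct |
|---|---|---|
| Fixed 4 | 33.3% | 70.8% |
| Random 4 and 6 | 5.7% | 69.0% |
| Random 4, 6 and 8 | 2.3% | 67.8% |

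Varying the size removes most of the certainty but little of the guessing advantage. Only a fixed order of envelope use removes the opportunity to act on a guess.

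**The case against.** The strongest reply is that the one-in-three figure describes an ideal observer. The article does not say that any therapist knows the block size, opens the envelopes or sees the whole sequence. Several physiotherapists and possibly several venues make complete knowledge by one person less likely. This stands: 33% is a ceiling.

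A second reply is that therapists do not decide enrolment. Eligibility and baseline precede randomization, and assessments belong to blinded evaluators. This also stands. A reader might infer that therapists could refuse or admit runners on a predicted arm, and the article does not support that. Only the order of attendance remains, and nothing in the article shows that therapists control it or have used it. VISA-A is measured at baseline, so an imbalance in it would be visible, and the group-by-time term compares change. Selection on something unmeasured would not be visible.

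A third reply concerns cost. Recruitment began in June 2024 and was expected to end by 31 October 2025, so little or none of the list may be left, and changing it means an amendment.

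A stronger reading is tempting on load testing. The interventions section says "Every two weeks, during the supervised session, a 10RM test will be performed to estimate 1RM and adjust training loads of all exercises accordingly", from which a reader might infer that the first test follows the opening of the envelope and distorts the loads that define the arms. The article does not give the order of those two steps, and the supplementary files are not shown. Both arms use 55% 1RM in weeks 1–2, and loads are reset from a new test every two weeks. Tests after the first session follow randomization under any scheme. This question is secondary and does not carry the point.

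**Conclusion.** The weakness is real but modest and conditional. A single fixed block of four, used at a session supervised by unblinded staff, allows deduction of up to one allocation in three (about 20 of 60) and best-guess accuracy of up to 71%. This rests on three conditions: the observer knows the block size, sees every earlier allocation in order, and knows where blocks begin. At half visibility the deducible share is about 8%. Harm further requires that the order of first sessions can be influenced, which the article neither states nor excludes. The documents do not show that concealment has failed or that bias has occurred. They do show that the stated procedure is not enough to claim that concealment is ensured.

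**What to change.** 1. At the end of the baseline assessment, bind each participant by enrolment number to the next sequentially numbered envelope. It can still be opened at the first session, but the order of attendance no longer decides the arm. The envelope of a runner who never attends should be retired and recorded, not reissued.
2. For any part of the list not yet used, starting at a block boundary, have the independent researcher generate it with randomly varying block sizes that are not disclosed to the therapists.
3. If recruitment has closed, report who held and opened the envelopes, what fixed the order of their use, and whether therapists knew the block size. Withdraw the statement that the envelopes ensured concealment.
4. State whether the first 10RM test comes before or after the envelope is opened.

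**Cost.** Items 1 and 2 need a protocol amendment and, for item 2, a new list. The statistical cost is a small possible imbalance. If the 60th participant falls halfway through a block of eight, all four of its used places could be the same arm, a split of 32 to 28. With sizes 4 and 6, the largest imbalance in an unfinished block at an even total is 2, a split of 31 to 29. Retired envelopes could add slightly to this. Items 3 and 4 cost only reporting.
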